## Abstract

**Background:**

Over recent decades, the prevalence of pediatric obesity has increased markedly in developed and developing countries, and the impact of obesity on health throughout the lifespan has led to urgent calls for action. Family-based weight management interventions that emphasize healthy lifestyle changes can lead to modest improvements in weight status of children with obesity. However, these interventions are generally short in duration, reported in the context of randomized controlled trials and there are few reports of outcomes of these treatment approaches in the clinical setting. Answering these questions is critical for improving the care of children with obesity accessing outpatient health services for weight management. In response, the CANadian Pediatric Weight management Registry (CANPWR) was designed with the following three primary aims:

1. Document changes in anthropometric, lifestyle, behavioural, and obesity-related co-morbidities in children enrolled in Canadian pediatric weight management programs over a three-year period;

2. Characterize the individual-, family-, and program-level determinants of change in anthropometric and obesity-related co-morbidities;

3. Examine the individual-, family-, and program-level determinants of program attrition.

**Methods/Design:**

This prospective cohort, multi-centre study will include children (2–17 years old; body mass index ≥85^th^ percentile) enrolled in one of eight Canadian pediatric weight management centres. We will recruit 1,600 study participants over a three-year period. Data collection will occur at presentation and 6-, 12-, 24-, and 36-months follow-up. The primary study outcomes are BMI z-score and change in BMI z-score over time. Secondary outcomes include anthropometric (e.g., height, waist circumference,), cardiometabolic (e.g., blood pressure, lipid profile, glycemia), lifestyle (e.g., dietary intake, physical activity, sedentary activity), and psychosocial (e.g., health-related quality of life) variables. Potential determinants of change and program attrition will include individual-, family-, and program-level variables.

**Discussion:**

This study will enable our interdisciplinary team of clinicians, researchers, and trainees to address foundational issues regarding the management of pediatric obesity in Canada. It will also serve as a harmonized, evidence-based registry and platform for conducting future intervention research, which will ultimately enhance the weight management care provided to children with obesity and their families.

## Background

Obesity has become a major public health issue in Canada. One in three Canadian children and youth are overweight or obese; a three-fold increase over the last three decades [1]. There is an increasing recognition of obesity-related health consequences during childhood into adulthood [2]. The development of obesity and its subsequent co-morbidities is influenced by a complex inter-relationship between factors that interact at multiple levels (e.g., physiology, individual activity, physical activity environment, food consumption, food production, individual psychology, and social psychology), which has been conceptualized as an obesity system map [3]. Examining and understanding how these factors relate to one another and change over time can help to tailor interventions to the unique needs of children with obesity and their families rather than a more traditional “one-size-fits-all” approach to weight management [3,4].

Lifestyle behaviour changes represent the foundation of pediatric weight management programs [5,6]. Several recent reviews have highlighted that comprehensive, family-based interventions are effective approaches for managing pediatric obesity [7-9]; however, intervention-mediated changes can vary substantially between individuals, and the causes of this variability remain understudied. Characterizing these variations and influences of potential determinants of obesity and obesity-related health outcomes at the individual-, family-, and program-level can help to guide the development of more effective interventions [10].

To improve weight management care, the individual factors that differentiate those boys and girls whose health outcomes improve *versus* those with no improvements or worsening health outcomes, as well as factors related to attrition and recidivism require additional study. Changes to lifestyle (nutrition, physical activity, sedentary activity) habits are usually promoted through individual and/or group-based counseling to encourage their adoption and maintenance [9,11]. The valuable outcomes of behavioral lifestyle interventions in the treatment of childhood obesity have been recently highlighted [8,12]. Limited research suggests that mental health issues predict poor response to the treatment of pediatric obesity [13]. Other factors predicting weight management program outcomes include participation in an exercise program at baseline [14], young age [15,16] with pre-pubertal children being more responsive than teens, and lower body mass index (BMI) z-score at baseline [17].

A number of family-level characteristics have been found to predict treatment outcomes in children with obesity [18]. A recent systematic review demonstrated that interventions that applied cognitive behavioral therapy for parents and children and the inclusion of rewards from parents were associated with improvements in children’s weight status. Furthermore, healthy diets among children were associated with high intakes of healthy foods and low intakes of unhealthy foods (e.g., fast foods) among family members, and less parental food restriction [19]. Although continued family attendance at clinical appointments [20,21] and high readiness to change lifestyle habits [22,23] are associated with health improvements in children with obesity, the factors that influence attendance and readiness remain poorly delineated.

At the program-level, limited research is available on the influence of program characteristics on obesity management and obesity-related health outcomes. Children and parents who complete a structured lifestyle and behavioural intervention achieve greater reductions in weight status than non-completers [8]. Intervention intensity (e.g., number of clinical contact hours) may be a key determinant of treatment efficacy, but the optimal number of contact hours is uncertain, and the nature of how and with whom these clinical hours are spent is unknown [8]. Our understanding of the effectiveness of program-related factors including intervention modality (e.g., group *vs* individual sessions), disciplinary approach (e.g., unidisciplinary *vs* multidisciplinary), and behavioural techniques (e.g., self-monitoring nutrition/physical activity habits, regular weighing, goal-setting) [24] in managing pediatric obesity remains incomplete. Multi-centre research will allow us to examine the influence of determinants of responsiveness to obesity management in diverse clinical environments that extend across cultures and contexts within the Canadian health care environment [25].

Despite evidence supporting the effectiveness of strategies to manage pediatric obesity [8], little evidence is available regarding the sustainability of changes in health outcomes achieved through behavioural interventions in pediatric obesity as highlighted in multiple systematic reviews [8,9] and reports [26]. A recent systematic review identified four trials that evaluated the maintenance of weight change after lifestyle and behavioural interventions and concluded that improvements in obesity status can be sustained over a 12-month follow-up period [8]. Children with obesity can lose and maintain weight loss up to five [15] and 10 years [27] following family-based lifestyle and behavioural interventions; however, these findings remain unique in the literature and fail to consider potential changes in other factors that are often targeted within interventions (e.g., nutrition, physical activity, cardiometabolic risk factors).

Related to sustainability of behavioural change and to program outcomes is the degree of attrition from clinical programs. Similar to attrition levels reported from adult obesity management programs, [28-30] dropping out of care is common in pediatric weight management programs, with reports suggesting 27–73% attrition [31]. Though not studied extensively, children’s age, mental health, and family socioeconomic status at presentation have been linked with attrition [30]. Descriptively, parents’ perception of the quality of the program at treatment onset is an important predictor of whether families will prematurely discontinue care [24].

With the aforementioned issues in mind, several questions remain unanswered; questions that are critical for improving the management of pediatric obesity. For instance: How do health outcomes beyond weight and BMI change during participation in weight management programs? What are the determinants of changes in body size and obesity-related co-morbidities? Are changes in obesity and obesity-related co-morbidities sustainable beyond 12 months in real-world, clinical settings? Are the determinants of change different for sustained *versus* transient changes in health outcomes? What individual, family, and contextual factors predict program attrition? To address these questions, the CANadian Pediatric Weight management Registry (CANPWR) study was designed with the following aims (Table 1):

**Table 1 T1:** **Objectives**, **hypotheses**, **measures**, **and methods of analysis**

**Objective**	**Hypothesis**	**Outcome measure ****(C = ****Continuous; ****B = ****Binary)**	**Methods of analysis**
**Primary**	Change in BMI z-score will be influenced by child/youth, family, and program characteristics consistent with our theoretical model	BMI z-score (C)	Hierarchical/multilevel modeling
Document changes in anthropometric, lifestyle, behavioural, and obesity-related co-morbidities in children enrolled in Canadian pediatric weight management programs over a three-year period			
**Secondary**	Change in cardiometabolic health outcomes will be influenced by child/youth, family, and program characteristics consistent with our theoretical model	Systolic and diastolic blood pressure (C)	Hierarchical/multilevel modeling
1) Document changes in anthropometric, lifestyle, behavioural, and obesity-related co-morbidities in children enrolled in Canadian pediatric weight management programs over a three-year period;			
		Blood glucose (Fasting & 2 hr post glucose load) (C)	
		Total cholesterol/HDL-C ratio (C)	
		Triglyceride (C)	
		Fitness (C)	
		Quality of Life (C)	
		Lifestyle behaviours (C)	
2) Characterize the individual-, family-, and program-level determinants of change in anthropometric and obesity-related co-morbidities;	Individual-, family-, and program-level determinants will be identified that predict sustainability of change from years 1 – 3.	BMI z-score (C)	Hierarchical/multilevel modeling
3) Examine the individual-, family-, and program-level determinants of program attrition.	Individual-, family-, and program-level determinants will differentiate those who dropped out of the program	Drop out from the program between enrollment and 1 year (B)	Hierarchical/multilevel modeling
			Logistic regression
**Exploratory analyses**	We will identify interaction terms between some individual, family and program determinants	All outcomes	Hierarchical/multilevel modeling
Identify what works best for what groups of individuals or families			
**Sensitivity analyses**	As above	All outcomes	1) Analysis with multiple imputation
1) Imputation methods			
2) All outcomes analyzed simultaneously to account for correlation among them			2) MANCOVA
			3) GEE
3) Serial correlation of all outcomes over time			

*MANOVA*: multivariate analysis of covariance.

*GEE*: Generalized estimating equations.

1. Document changes in anthropometric, lifestyle, behavioural, and obesity-related co-morbidities in children enrolled in Canadian pediatric weight management programs over a three-year period;

2. Characterize the individual-, family-, and program-level determinants of change in anthropometric and obesity-related co-morbidities;

3. Examine the individual-, family-, and program-level determinants of program attrition.

The following hypotheses will be tested:

### Primary hypothesis

1. Change in children’s BMI z-score will be influenced by individual-, family-, and program-level determinants.

### Secondary hypotheses

1. Individual-, family-, and program-level determinants will influence changes in anthropometric, lifestyle behaviour and cardiometabolic health measures over a three-year period.

2. Individual-, family-, and program-level determinants will influence the sustainability of change in BMI z-score over a three-year period.

3. Individual-, family-, and program-level variables will predict program attrition.

## Methods/Design

### Study design

This prospective cohort, multi-centre study will include children (2–17 years old; BMI ≥85^th^ percentile) who consent to participate and are enrolled in one of eight participating weight management centres affiliated with children’s hospitals in Hamilton, ON (McMaster Children’s Hospital; coordinating site); Vancouver, BC (BC Children’s Hospital); Edmonton, AB (Stollery Children’s Hospital); Toronto, ON (The Hospital for Sick Children and North York General Hospital); Ottawa, ON (Children’s Hospital of Eastern Ontario); and Montreal, QC (Montreal Children’s Hospital and CHU Sainte Justine). The study centres will continue their current program [25], but data collection for outcomes and determinants will be standardized amongst centres. It should be noted that all of these programs are in urban centres, are in secondary or tertiary care environments, may have relatively wide geographic referral areas and are funded under a single payer system. The current manuscript has been written in accordance with the Strengthening the Reporting of Observational Studies in Epidemiology (STROBE) guidelines and checklist [32].

### Study population

All children and youth enrolling in a participating tertiary care weight management centre will be eligible to participate. Beginning in 2013, we will recruit 1,600 study participants over three years and will follow them for up to three years. Exclusion criteria are children younger than 2 years or older than 17 years, age- and sex-specific BMI < 85^th^ percentile and lack of fluency in spoken and written English or French.

### Ethics approval & confidentiality

Research ethics and administrative site approvals were received at all eight participating sites prior to study initiation. Collected information will remain confidential; individual names will not be used for any purpose. Each participant will be assigned a unique ID number, which will be used as the participant’s identifier. Records that identify participants will be kept confidential and are only available to the research team for contact purposes. All participant study binders will be stored in lockable filing cabinets at each site, which are under the supervision of the local site leads. Any data presented publically or published as a result of this research will ensure participant anonymity.

### Measurements

Health outcomes and purported determinants that are evidence-based and measured at each centre with methodologies that have been standardized and harmonized through the initial phase of CANPWR will be included. The primary outcome is change in BMI z-score (WHO definition). Secondary health outcomes include absolute BMI [33], waist circumference, hip circumference, cardiometabolic measures (blood pressure, glycemia (fasting and two-hour blood glucose), lipid profile (total cholesterol/high density lipoprotein cholesterol ratio, and triglyceride), liver enzymes (AST, ALT)), aerobic fitness and quality of life (Peds QL). The determinants to be evaluated for their influence on change of the primary and secondary outcomes include individual, family, and program characteristics. Characteristics of the *Individual* include demographic (e.g. age, sex, ethnicity, immigrant status), biological (e.g. BMI z-score at baseline, medical history including medication use and other health disorder(s)) and life style behaviours (e.g. dietary intake, family eating patterns, sedentary activity, sleep, readiness to change, nutrition and physical activity habits). *Family* characteristics include family health (e.g. parental weight status, family history of type 2 diabetes, coronary heart disease), socioeconomic status, family structure (e.g. number of people living in household), and readiness to change nutrition and physical activity behaviours at baseline. *Program* characteristics will include intervention modality (individual *vs* group-based care), parental participation, participant satisfaction with care, proportions of clinical time families spend with different disciplines, number of clinic hours attended, clinical status at time of study visit (active, inactive or discharged), and adherence to scheduled clinic visits (proportion of planned visits attended).

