### Statistical power

Given a sample size of 1,600 and 41 variables or determinants to be included, the ratio of participants to variables is 39:1. Previous studies have shown that a fitted regression model is likely to be reliable and stable when the number of independent predictors is less than the total sample size divided by 20 [40]. Considering 40%, 25% or 15% dropout (n = 960, 1,200, 1,360 respectively), a two-sided test with significant level α = 0.05/4 = 0.0125 gives 90% power to detect a small R-square 0.0313 -0.0442 for 41 determinants. Thus, we have high power to test the effects of the described variables. For secondary hypothesis one (Table 1), we intend to examine three additional outcomes. To account for multiple hypothesis testing two-tailed α = 0.0125, we will continue to have power exceeding 90% to examine the influence of the determinants on the outcome at one year. For secondary hypothesis two, we intend to examine the determinants for sustainability of weight loss. To do so, we will examine the determinants for maintenance or decline of BMI z-score from year one to year two. If we conservatively estimate that at least 30% will have an increase in BMI z-score over that time period, we have 90% power to detect a variable that will increase this by 1.3 fold – and this is true even if we have 40% drop out from our study. Similarly, if the proportion of participants whose BMI z-score increases from year one to year two is higher, our power would be > 90%. Findings from several published trials suggest these assumptions are appropriate [21,41]. For secondary hypothesis three, we will examine the determinants of program drop out within one year of enrollment. We are sufficiently powered to detect an OR of 1.2 if 25% or more of those who commence a program drop out, and to detect an OR of 1.3 if only 15% drop out of the program.

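### Baseline individual and family determinants appear to share one regression with post-enrolment engagement variables, so their coefficients would omit any effect acting through engagement and could be attenuated

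*Protocol article*

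**What the plan says.** Under Measurements the protocol article gives one list of determinants for all outcomes: "The determinants to be evaluated for their influence on change of the primary and secondary outcomes include individual, family, and program characteristics". The individual and family entries are mostly known at entry (age, sex, ethnicity, baseline BMI z-score, socioeconomic status, family structure, readiness to change). The program entries mix intervention modality with variables that can only be known later: clinic hours attended, clinical status at the visit, the proportion of planned visits attended, satisfaction, parental participation and the split of clinical time between disciplines.

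Statistical analysis relates outcomes to all three levels by multilevel modelling. It describes no order of entry, and its only rule for removing a variable is a variance inflation factor above 10.

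Statistical power opens with "Given a sample size of 1,600 and 41 variables or determinants to be included, the ratio of participants to variables is 39:1". It supports this with a rule of thumb that uses a divisor of 20 ("a fitted regression model is likely to be reliable and stable when the number of independent predictors is less than the total sample size divided"), and gives 90% power for an R-square of 0.0313 to 0.0442 over 41 determinants.

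The Background says that children's age, "mental health, and family socioeconomic status at presentation have been linked with attrition", and that "continued family attendance at clinical appointments [20,21] and high readiness to change lifestyle habits [22,23] are associated with health improvements in children with obesity". Secondary hypothesis 3 is that individual, family and program variables predict attrition.

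**The concern.** The primary hypothesis, like the Measurements section, is about which determinants influence change. If a family factor acts partly by keeping the child in care, its influence on BMI z-score change includes that route. A regression that also contains hours attended, visit adherence and clinical status holds the route fixed, and the coefficient then shows only what remains.

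Clinical status shows the difficulty most clearly. Whether a child is active, inactive or discharged is close to the attrition outcome of secondary hypothesis 3, yet it is listed as a determinant beside the factors expected to predict that outcome. Engagement is also likely to vary in the analysed data, because Data collection arranges separate research visits for families who stop attending.

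What is at stake is the reading of individual and family coefficients under the primary hypothesis and aim 2. Factors that work through engagement could be reported as weak or unimportant, although the Discussion intends the results to inform how services are modified. The point concerns the other determinants' coefficients. It does not ask whether the attendance coefficient is itself causal.

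**Working it through.** **1. Does the plan's own figure describe one model?** The inputs are from Statistical power: 41 determinants, "Considering 40%, 25% or 15% dropout (n = 960, 1,200, 1,360 respectively"), and "a two-sided test with significant level α = 0.05/4 = 0.0125". Take the overall F test of R-square with p = 41, denominator degrees of freedom n − 42 and noncentrality n·R²/(1 − R²), and solve for 90% power.

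| n | Detectable R² | Stated R² | Power at stated R² |
|---|---|---|---|
| 960 | 0.0439 | 0.0442 | 90.3% |
| 1,360 | 0.0311 | 0.0313 | 90.3% |

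The stated range reproduces as a single 41-df regression. The ratio 1,600/41 = 39 and the N/20 rule (1,600/20 = 80; 960/20 = 48) also treat the 41 as one set of predictors.

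**2. Would the collinearity rule catch the problem?** If a baseline factor and attendance correlate at 0.3, the variance inflation factor for that pair is 1/(1 − 0.3²) = 1/0.91 = 1.1, far below 10. It would not.

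**3. What happens to a baseline coefficient?** The documents give no path sizes, so these are assumptions on standardised scales: a is the path from baseline factor to attendance, b from attendance to outcome, and c the direct path. Without attendance in the model the coefficient is c + a·b. With attendance in the model, and no unmeasured common cause, it is c. The power figures below come from 2,000 simulated datasets per row, n = 960, two-sided alpha 0.05 per coefficient.

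| a | b | c | Without attendance (power) | With attendance (rejection rate) |
|---|---|---|---|---|
| 0.3 | 0.3 | 0 | 0.09 (80%) | 0 (5%) |
| 0.3 | 0.3 | 0.09 | 0.18 (100%) | 0.09 (80%) |
| 0.1 | 0.3 | 0.10 | 0.13 (98%) | 0.10 (91%) |

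For the first row, the approximation Φ(a·b·√n − 1.96) gives Φ(0.09 × 30.98 − 1.96) = Φ(0.83) = 80%. At the protocol's alpha of 0.0125 the critical value is 2.498, so the power without attendance is Φ(2.79 − 2.50) = Φ(0.29), about 61%.

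With c = 0 and each path between 0.2 and 0.4, the coefficient lost ranges from 0.2 × 0.2 = 0.04 to 0.4 × 0.4 = 0.16.

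**4. When could the sign change?** Add an unmeasured common cause with effect 0.4 on both attendance and outcome, with a = b = 0.3 and c = 0. The adjusted coefficient becomes −a × 0.4 × 0.4/(1 − a²) = −0.048/0.91 = −0.053, against 0.09 without attendance. In simulation it was significant in 43% of datasets. In the other cases above, which have no such common cause, the sign did not change.

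**5. Does a baseline model weaken the overall test?** The number of baseline determinants is not given, so it is assumed. Detectable R² at 90% power and alpha 0.0125:

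| Determinants | n = 960 | n = 1,200 | n = 1,360 |
|---|---|---|---|
| 41 | 0.0439 | 0.0352 | 0.0311 |
| 38 | 0.0427 | 0.0342 | 0.0302 |
| 35 | 0.0413 | 0.0332 | 0.0293 |
| 30 | 0.0390 | 0.0313 | 0.0276 |

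Fewer determinants make a slightly smaller R² detectable.

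**The case against.** A reader might infer that the protocol orders all 41 determinants into one model at once, that it names attendance as the step between family factors and weight change, and that real determinants will therefore vanish or reverse. The text does not go that far:

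- **Simultaneous entry** is a strong inference from the power section. The 41 are not itemised, and an analysis plan that is not shown could stage the models.
- **Attendance as a mediator** is never stated. The two links are given separately, as associations or hypotheses, with attrition standing in for attendance in the first. The Background adds that attrition has not been studied extensively and that the factors behind attendance are poorly delineated.
- **Loss or reversal** depends on assumptions. Full loss needs almost no direct effect. A sign change needs an opposing direct effect or an unmeasured common cause, and readiness to change, which is on the determinant list, measures part of the obvious candidate (motivation). Factors unrelated to attendance are little affected.

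It can also be said that Statistical analysis promises measures of association, for which mutually adjusted coefficients are a legitimate target, and that aim 3 models dropout separately.

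These arguments limit the size of the point but do not remove it. The article itself fixes the mixed list, powers the joint model and uses the word influence, so a plan that follows it inherits the problem. The attrition analysis would show that a factor predicts dropout, but not what that factor does to BMI z-score change.

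**Conclusion.** The concern holds in a limited form. The power section treats the 41 determinants as one regression, and the listed determinants include variables known only after enrolment. If engagement carries part of the effect of individual and family factors, which the protocol's own background makes plausible, their coefficients in that model are not total effects. They could be attenuated, or lost where the effect runs almost wholly through engagement.

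On the assumed paths the change ranges from small (0.13 to 0.10) through halving (0.18 to 0.09) to complete (0.09 to 0). These sizes are illustrations and not estimates for this cohort. The conclusion rests on the reading that the listed engagement variables are among the 41 and are entered together with the baseline factors. The overall R-square test and the attrition analysis do not depend on it.

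**What to change.** For each outcome, state two models and say which coefficients are reported from which.

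1. **Baseline model:** individual and family determinants at their baseline values, plus program features fixed at entry, such as modality. Report the influence of baseline factors from this model.
2. **Engagement model:** add all post-enrolment program variables, namely hours attended, visit adherence, clinical status, satisfaction, parental participation and proportion of time by discipline. Report their coefficients as engagement associations, and state that the baseline coefficients in this model are not total effects.

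The second model keeps the joint 41-determinant regression, so the stated power calculation still applies to it. No new data are needed. The cost is some wording in the analysis plan, plus one extra model and a longer results table per outcome.

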### Data collection

Information will be retrieved at the baseline visit, followed by 6-, 12-, 24-, and 36-months follow-up. Data collection will be done within the weight management centres, all of which are in ambulatory environments. A comprehensive questionnaire will be administered and includes information on demographics, child lifestyle behaviours, and readiness to change lifestyle habits. Many demographic and lifestyle-related questions were derived from the *Canadian Health Measures Survey*[34], which was done to enable comparisons between study participants and a nationally-representative sample of Canadians. Family eating patterns will be evaluated using a validated questionnaire [35] that has predicted changes in BMI z-score amongst children enrolled in a weight management program. To promote participant retention, site specific newsletters will be periodically mailed or emailed to families. This newsletter will serve as a reminder to participants of their upcoming appointment, will encourage families to contact CANPWR researchers if their contact information changes during the study and will update them on the study progress. If study participants stop attending the weight management program (either inactive or discharged), a research visit separate from clinical care will be arranged to enable data collection. When data are missing or if families discontinue study participation, whenever possible, data will be retrieved from children’s medical records to populate study-specific case report forms. Participating families will receive up to $100 in the form of gift cards as tokens of appreciation. All de-identified study data will be entered into a secure, encrypted *iDataFax* web-enabled software application for central storage at the Population Health Research Institute (PHRI) (McMaster University; Hamilton, ON). A complete list of the contributors to the CANPWR study including the Central Coordinating Site and the research staff at each site is listed in Additional file 1.

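### The only listed program-level determinants include variables that restate or are cut short by drop-out, and nothing keeps them out of the attrition model

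*Protocol article*

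**What the plan says.** Secondary hypothesis three reads "Individual-, family-, and program-level variables will predict program attrition". Table 1 repeats it as "Individual-, family-, and program-level determinants will differentiate those who dropped out of the program", with a binary outcome running from enrollment to one year and analysis by multilevel modeling and logistic regression. The Statistical power section confirms the horizon: "we will examine the determinants of program drop out within one year of enrollment".

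The abstract (Methods/Design) puts change and attrition under the same three levels: "Potential determinants of change and program attrition will include individual-, family-, and program-level variables". The program level is itemised in one place only, the Measurements section. There it consists of modality, parental participation, satisfaction with care, shares of clinical time by discipline, and "number of clinic hours attended, clinical status at time of study visit (active, inactive or discharged), and adherence to scheduled clinic visits". Adherence is defined as the proportion of planned visits attended.

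The Data collection section shows what two of the status categories mean: "If study participants stop attending the weight management program (either inactive or discharged), a research visit separate from clinical care will be arranged". The Statistical power section counts 41 determinants and mentions no smaller or different set for attrition.

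**The concern.** A predictor of drop-out has to be known before drop-out happens. On the program list, only modality is clearly fixed at entry. Clinical status read at 12 months is close to the outcome itself: a child who has left is recorded as inactive. Total hours attended are lower because the child left. The proportion of planned visits attended behaves the same way if visits planned after exit stay in the denominator.

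Two things are at stake. First, these variables would come out as strong determinants of attrition in any data, whatever the programs do. Second, total hours can distort the odds ratios of other variables. At equal total hours, a child in a program with more hours per month must have been enrolled for less time. A feature that merely raises contact hours then looks as if it drives families away. Attrition is one of the article's three aims, and its results are meant to guide how programs are run.

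**Working it through.** **Passages side by side.** Outcome: drop-out by one year (Table 1). Predictors: all three levels (abstract, Secondary hypotheses, Table 1). Content of the program level: the Measurements list, the only one given. Meaning of inactive or discharged: no longer attending (Data collection). Restriction of hours, status or adherence to a time before drop-out: none. The wording 'at baseline' is attached only to BMI z-score and to family readiness to change. The one stated screen, VIF > 10 (Statistical analysis), compares predictors with each other and cannot detect a predictor that overlaps the outcome.

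**The plan's own figures.** For 41 determinants, two-sided α = 0.0125 and 90% power, a noncentral F test with 41 numerator df and λ = n·R²/(1−R²) gives R² = 0.0311 (n = 1,360), 0.0352 (n = 1,200) and 0.0439 (n = 960). The article states 0.0313 to 0.0442, so its figure reproduces with a single set of 41.

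For attrition the article names an OR of 1.2 at 25% drop-out. Taking the OR per SD and n = 1,600, power = Φ(√(n·p(1−p))·ln OR − z):
- √(1,600 × 0.25 × 0.75) = 17.32, and 17.32 × ln 1.2 = 3.158.
- At α = 0.05: Φ(3.158 − 1.960) = 88.5%.
- At α = 0.0125: Φ(3.158 − 2.498) = 74.5%.

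The article gives no power for this OR, so nothing here is disputed. The 1.2 serves as the yardstick below.

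**Illustration 1: are attendance totals predictive when nothing causes drop-out?** The documents give no hours or visit counts, so these inputs are assumptions: N = 1,600; drop-out 15%, 25% or 40%, at a uniform time over 12 months and independent of every characteristic; 12 planned visits; 1.5 or 2.0 clinic hours per month by modality; 400 runs per scenario.

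| Quantity, no true determinant | Result | Rejected at α = 0.0125 |
|---|---|---|
| Total hours | OR 0.14 to 0.17 per SD, AUC about 0.84 | 100% |
| Adherence, all 12 planned visits in the denominator | OR 0.08 to 0.12 per SD | 100% |
| Adherence, only visits planned while enrolled | small artefact | 2 to 3% (7 to 12% at 0.05) |
| Modality, not adjusted for hours | null | 0.5 to 1.5% |
| Modality, adjusted for total hours | false OR 2.3 to 2.4 | 99.5 to 100% |
| Hours, adherence or hours-adjusted modality, first 3 months, among those still attending | null | about 0.75 to 2% |

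**Illustration 2: a weaker link with hours.** Assumptions: n = 1,600; 25% drop-out, uniform over the year; hours = time enrolled × lognormal intensity with log-SD 0.3 (range 0.2 to 0.5). A determinant x has no effect on drop-out but raises hours by 5% per SD. The model is logit P(drop-out) = a + b·x + c·hours. For the same hours and the same personal intensity, one SD more of x implies 1/1.05 = 0.952 of the time enrolled, which pushes b above zero.
- With hours in the model: OR about 1.21 (1.10 to 1.39). Rejected in 77% (28 to 99%) at 0.05 and in 54% (16 to 95%) at 0.0125. The top of each range belongs to log-SD 0.2, where hours track time enrolled most closely.
- Without hours: OR 1.00, rejected in about 5% at 0.05.
- A null baseline variable unrelated to hours kept its error rate.

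**The case against.** The strongest reply is that the article never says these three variables enter the attrition model. The Measurements section introduces its list with "The determinants to be evaluated for their influence on change of the primary and secondary outcomes include individual, family, and program characteristics", and drop-out is not among the outcomes named there. For change in BMI z-score, hours and adherence are sensible measures of dose. An article may also leave the covariates of one secondary model to a fuller plan.

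The first part stands: entry into the attrition model is an inference, and the point is worded as one. It is nevertheless the natural reading, because the abstract pairs change and attrition under the same levels, attrition is itself a secondary objective in Table 1, and no other program list exists. The second part carries less weight. The article names both the predictors and the outcome, and following its text gives a circular result, so this is more than an omitted detail.

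A reader might infer that hypothesis three as a whole is confirmed by construction. The documents do not support that: individual- and family-level predictors such as age, socioeconomic status or readiness are not circular. Nor are all three program variables equivalent to drop-out. A discharged child need not have dropped out, status is recorded at each study visit and not only at 12 months, and adherence is mechanical only if visits planned after exit are counted.

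**Conclusion.** The point holds in limited form. If the listed program variables enter the attrition model as the text suggests, status and total hours, and adherence under one choice of denominator, would make the program-level part of hypothesis three largely self-fulfilling. A null feature that raises hours could show an OR of about 1.1 to 1.4 for 5% more hours per SD, against a target OR of 1.2. With a larger gap in hours, as between the two assumed modalities, the false OR is 2.3 to 2.4. These sizes rest on assumed hours, visit counts and drop-out timing. The direction needs only that hours accumulate with time enrolled.

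The primary hypothesis, secondary hypotheses one and two, the sample size and the data collection are unaffected. One of three stated aims is affected, so this should be fixed.

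**What to change.** State for the attrition model that:
- determinants are limited to those fixed at or before entry: baseline individual and family variables, modality, and planned program intensity;
- clinical status is not a predictor;
- hours, adherence and satisfaction are used only from a fixed early window (for example the first 3 months), among children still active at its end, to predict later drop-out (landmark analysis).

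The same variables may stay in the models for change in BMI z-score.

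This is a change of wording in the analysis plan. It has two costs. Whole-period attendance is no longer reported as a determinant of attrition. The landmark part also leaves out early drop-outs: with uniform timing, 25% drop-out and a 3-month window, that is 1,600 × 0.25 × 3/12 = 100 of the 400 drop-outs. Those children still count in the model with entry-fixed determinants.
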